8.8 Confidentiality

8.9 Archiving

**9. PUBLICATIONS**

**10. BIBLIOGRAPHY**

**1. STATE OF SCIENTIFIC KNOWLEDGE**

Anal incontinence is a public health problem because of its prevalence (Denis, 1992). Anal incontinence includes the accidental passing of solid or liquid stools via the rectum (fecal incontinence) and the involuntary leakage of gas (flatus incontinence). Flatus incontinence is the most common type of anal incontinence, with a prevalence estimated at approximately 33% in the general adult population (Damon, 2006). Although flatus incontinence appears to have less impact upon quality of life than fecal incontinence (Boreham, 2005), it is an embarrassing and socially restricting problem (Steinberg, 2009; Meyer, 2015). The management of flatus incontinence is challenging. Conservative medical (biofeedback) and surgical (sacral nerve stimulation, artificial bowel sphincter) strategies used to treat fecal incontinence are often disappointing in terms of reducing gas leakages (Michot, 2003; Leroi, 2009). Medications such as simethicone/activated charcoal are used to relieve gaseous symptoms, but the few studies on their efficacy have reported contradictory results (White, 1991; Friis, 1991).

Flatus incontinence is associated with anal sphincter weakness and can be exacerbated by excessive rectal gas production (Di Stefano, 2000), which can be caused by small intestinal bacterial overgrowth (SIBO). SIBO is defined as a bacterial population in the small intestine exceeding 10^5^–10^6^ organisms/mL (Simren, 2006). Symptoms of SIBO include diarrhea, weight loss, anemia, and intestinal malabsorption. Gastrointestinal tract surgeries that create blind loops (jejuno-ileal bypass, end-to-side enteroenteric anastomosis) as well as small bowel motility disorders (sclerodermia, intestinal pseudo-obstruction) predispose to bacterial stasis and overgrowth. SIBO has also been observed in patients with irritable bowel syndrome or dyspepsia (Pimentel, 2000; Pimentel, 2003). SIBO is generally diagnosed using glucose hydrogen (H_2_) and methane (CH_4_) breath tests.

The principle of the test is as follows: exhaled H_2_ and CH_4_ are produced by the bacterial metabolism of ingested glucose in the colon. Normally, ingested glucose is totally absorbed in the small intestine and does not reach the colon. Absorbed glucose is not metabolized to produce H_2_ or CH_4_. In the case of SIBO, bacteria metabolize glucose before it is absorbed, producing H_2_ or CH_4_ that appears early in breath samples. Since it has a sensitivity of approximately 80%, the glucose breath test is more commonly used to diagnose SIBO than endoscopic small bowel aspirate cultures (Fine, 1999). Although antibiotics can be used to treat SIBO, there is no consensus about the type of antibiotics to use, how often they should be used, or whether a single antibiotic or whether several alternating or combined courses of antibiotics should be prescribed (Quigley, 2006]. However, norfloxacin, amoxicillin-clavulanic acid, and metronidazole appear to be good therapeutic options (Quigley, 2006].

We anticipate that the negativation of glucose breath test results in patients with flatus incontinence, which indicates that SIBO has been successfully eradicated, will result in a symptomatic improvement of their flatus incontinence.

**2. AIMS OF THE STUDY**

The aims of the study are to compare the efficacies of a conventional therapy and of an antibiotic therapy for treating SIBO diagnosed by the glucose breath test and to determine whether the antibiotic treatment improves flatus incontinence.

**3. METHODS**

**3.1 Outcome measures**

The main outcome measure will be the daily number of gas leakages.

The secondary endpoints will be:

- The fecal incontinence severity score
- The quality of life scores
- The frequency of fecal incontinence episodes
- The frequency of urgency episodes
- The frequency of bowel movements
- The symptom scores (abdominal pain, borborygmi)

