If a patient displays secondary effects or develops an allergy to metronidazole or Carbosylane^®^, he/she will be excluded from the study and will be replaced by another patient. Given the number of patients that will potentially be excluded from the study following their inclusion, we plan on recruiting 50 patients in order to maintain a 20-patient cohort for each experimental arm (Carbosylane^®^ and metronidazole).

The main primary outcome will be the percentage decrease in the mean daily number of gas leakages reported in the 3-day diaries that will be completed before (baseline) and at the end of the 10-day treatment period and before the regimen performed prior to the glucose breath test. A positive clinical response will be defined as a greater than 50% reduction in the mean daily number of gas leakages.

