**4.2 Data collection**

**Demographic data, clinical symptoms**: All the data will be collected and will be compiled in individual patient case report forms (CRFs), which will be archived in the investigation center. Information will be collected by the research staff or the investigator from the patient and from his/her medical record.

**Bowel diary**: Three-day bowel diaries describing flatus incontinence episodes (main criterion), bowel movements, urgency episodes, and fecal incontinence episodes will be completed by each patient. The treatment and the secondary effects will be noted in the diaries. The bowel diaries will be completed at the beginning of the study before the treatments and at the end of the treatments.

**Fecal incontinence severity score**: The Cleveland Clinic score will be used (Jorge, 1993). Scores will be recorded at the beginning and at the end of the study.

**Quality of life scores**: Quality of life will be evaluated using two questionnaires that have been validated in French. One is specific for fecal incontinence (FIQL) [Rullier, 2004] while the other is specific for functional digestive disorders (GIQLI) [Slim, 1999]. These questionnaires will be completed at the beginning and at the end of the study.

**Symptom scores**: The patients will be asked to subjectively rate the intensity of each symptom (bloating, abdominal pain, borborygmi) using the following scores: 0 = none, 1 = mild, 2 = moderate, and 3 = severe. The means of the scores attributed daily for 3 days will be calculated to obtain the final scores for the symptoms at the beginning and at the end of the study.

**Treatment compliance**: Treatment compliance will be evaluated by counting the number of tablets remaining at the end of the study.

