**4.3 Data analysis**

Results will be expressed as means ± standard deviation. The mean number of flatus incontinence episodes during the 3 days prior to and at the end of the treatment will be calculated. The difference between the mean number of flatus incontinence episodes before and during the treatment and the percentage decrease in the mean daily number of flatus incontinence episodes will be calculated and will compared between the two groups of patients (metronidazole and Carbosylane^®^ groups). The severity scores, quality of life scores, mean number of bowel movements, fecal incontinence episodes, urgency episodes, and symptomatic scores will be compared between the two groups.

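### Section 3.6 makes the percentage decrease in gas leakages primary, but 3.1 names only the daily number, and 4.3 compares two unranked change measures and words the post-treatment window two ways

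*Protocol*

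**What the plan says.** Four sections of the protocol describe the main outcome.

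- **3.1 Outcome measures:** "The main outcome measure will be the daily number of gas leakages". No time point or change measure is attached. The list of secondary endpoints that follows contains no other summary of gas leakage.
- **3.6 Study design and randomization:** "The main primary outcome will be the percentage decrease in the mean daily number of gas leakages reported in the 3-day diaries". The diaries are those completed at baseline and at the end of the 10-day treatment. The next sentence reads: "A positive clinical response will be defined as a greater than 50% reduction in the mean daily number of gas leakages". This response is not called primary, secondary or descriptive.
- **4.2 Data collection:** flatus incontinence episodes in the three-day diary are marked as the main criterion. Only the variable is named.
- **4.3 Data analysis:** "The mean number of flatus incontinence episodes during the 3 days prior to and at the end of the treatment will be calculated". The next sentence says what is compared between the groups: "The difference between the mean number of flatus incontinence episodes before and during the treatment and the percentage decrease in the mean daily number" of episodes. The two measures are joined by a plain conjunction. The response from 3.6 does not appear.

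Section 4.1 calls the trial a pilot study and describes the 20 patients per group as an arbitrary number.

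**The concern.** The absolute difference and the percentage decrease come from the same diaries but answer different questions. The absolute difference is driven by patients who start with many leakages. The percentage decrease divides each patient's change by that patient's own baseline, so patients who start with few leakages count as much as those who start with many. With 20 patients per arm the two can point to different arms.

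A reader of 3.6 would expect the percentage decrease to decide the trial. A reader of 4.3, the only analysis section, would find the absolute difference given equal standing. If the more favourable one may be reported as the main result, the false-positive rate of the headline comparison rises above that of a single test, and nobody can later tell from the protocol which was intended.

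The post-treatment window adds a second choice, because 4.3 first places the count at the end of treatment and then speaks of the period during treatment.

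**Working it through.** **1. The texts side by side**

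| Section | Variable | Measure | Post-treatment window | Status given |
|---|---|---|---|---|
| 3.1 | gas leakages per day | none | none | main |
| 3.6 | mean gas leakages per day | percentage decrease | end of the 10-day treatment | main primary |
| 3.6 | mean gas leakages per day | reduction above 50% | same diaries implied | none |
| 4.2 | flatus episodes in diary | none | end of treatment | main criterion |
| 4.3 | mean flatus episodes | absolute difference | end of, then during, treatment | none |
| 4.3 | mean daily flatus episodes | percentage decrease | not restated | none |

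Sections 3.1 and 4.2 are compatible with 3.6 if they name only the variable. Sections 3.6 and 4.3 do not match: one measure is primary in 3.6, and two are on equal footing in 4.3.

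**2. Why the two measures in 4.3 can disagree**

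Let B and F be a patient's mean daily count at baseline and at the end of treatment.

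- Absolute difference: D = B - F.
- Percentage decrease: P = 100 x (B - F)/B = 100 x D/B.

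P weights each patient's D by 1/B, so the two group comparisons use different weights whenever B varies between patients.

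**3. The plan's own figures**

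There is no power calculation to reproduce, since 20 per group is declared arbitrary. Recruiting 25 per arm agrees with 20/(1 - 0.20) = 25, an implied loss of 20%. Alpha, test, effect size and standard deviation are not stated.

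**4. Cost of a free choice when the arms do not differ**

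An upper reference, if k tests at 0.05 were independent, is 1 - 0.95^k:

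- k = 2: 9.75%
- k = 3: 14.3%
- k = 4: 18.5%

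The measures share the same diaries and are correlated, so the real figure is lower and has to be simulated.

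The only input taken from the protocol is 20 per arm with 3-day diaries. Everything else is assumed: two-sided 0.05, t-tests for the continuous measures, Fisher's exact test for the response, and Poisson counts with extra between-patient variation. The main model has a mean of 2-10 leakages a day, log-SD 0.8 and baseline-to-end correlation 0.5-0.7. It was run twice: with an end-to-baseline ratio of 1 or 0.7 (12 scenarios, 2,000 runs each), and with a 30% fall in both arms (4,000 runs per scenario). A second model used means of 5 or 10 a day, a different between-patient distribution and an average 30% fall in both arms (six scenarios, 4,000 runs each).

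| Chance that at least one p < 0.05 | Main model, first set | Main model, second set | Second model |
|---|---|---|---|
| Absolute difference or percentage decrease | 6.1-7.6% | 6.3-7.5% | not run |
| Adding the >50% response | 7.5-9.2% | 7.7-8.9% | 6.8-9.2% |
| Adding the end-of-treatment count | 10.9-12.4% | 11.2-12.6% | 8.8-13.0% |

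For comparison, each measure fixed in advance under the second model gave 3.8-5.0% (absolute difference), 3.9-4.8% (percentage decrease), 1.8-2.5% (response) and 3.4-4.8% (end count). Under the main model, the absolute difference and the percentage decrease favoured opposite arms in 26-31% of null trials.

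**The case against.** The best defence is that the protocol does choose. Section 3.6 labels the percentage decrease as the main primary outcome and ties it to diaries at baseline and at the end of the 10-day treatment. No other section calls a different change measure primary. Sections 3.1 and 4.2 can fairly be read as naming the variable, with 3.6 supplying the measure. The trial is a pilot with no stated alpha or success rule, and a statistical analysis plan that is not shown may fix the test.

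Much of this stands, and it limits the point. A reader might infer that the protocol sets up four rival primary outcomes with nothing to rank them. The text does not support that. The end-of-treatment count is only to be calculated, not compared between groups. The response is defined but never called primary, and 4.3 does not plan to compare it. Nor can one say that the protocol breaks a 5% error rate, because it claims none.

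What does not stand is the idea that the mismatch is analysis detail to be settled elsewhere. The protocol's own analysis section gives a second measure the same standing as the one 3.6 calls primary and words the window in two ways. A later document could settle that only by overriding one section. The pilot label lowers the confirmatory weight, but section 2 states a comparative efficacy aim and section 9 commits to publication.

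**Conclusion.** The inconsistency is real and narrow. Section 3.6 names a primary measure, 3.1 does not repeat it, and 4.3 sets an unranked rival beside it. The response above 50% has no place in the hierarchy, and the post-treatment window is worded in two ways.

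On the text as it stands, the firmest figure is the one for the two measures that 4.3 actually compares: a false-positive chance of about 6-8% instead of about 5%. The figures of 8-9% and 11-12% apply only if the response, and then also the end value, could be promoted to the main result, which the protocol does not plan. All of these figures depend on assumed diary distributions and an assumed two-sided 0.05. The second model shows how far the four-measure figure can move, from about 9% to 13%.

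The inflation is modest. The practical harm is that the direction of the headline result could depend on which measure is picked.

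**What to change.** Before the data are seen, state one primary measure and one window, the 3-day end-of-treatment diary, in the same words in 3.1, 3.6 and 4.3. Remove the wording in 4.3 that refers to the period during treatment. Label the remaining measures and the response above 50% as secondary.

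Either of two choices would do:

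- **Keep the percentage decrease.** This cures the inconsistency with the least change, since 3.6 already calls it primary.
- **Use the end-of-treatment mean daily count, compared between arms with adjustment for the baseline diary.** This is a sound alternative and uses data already collected. Its small cost is that it replaces the measure 3.6 now labels primary.

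Either way the cost is a few sentences of protocol text, with no change to diaries, visits or sample size.

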**3.2 Inclusion criteria**

The inclusion criteria will be:

1. Patients over 18 years of age who were referred to our center for isolated or predominant (in the case of associated fecal incontinence) flatus incontinence
2. Patients who have a positive glucose breath test
3. Patients who have read and signed the informed consent
4. Patients who are affiliated with the national healthcare system
5. Patients who go to the inclusion visit

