**3.4 Patient selection**

All patients who consult for flatus incontinence or for predominant flatus incontinence in the case of associated fecal incontinence (i.e., occasional fecal incontinence episodes with fewer than one episode per month) will be asked if they are interested in participating in the study.

Each patient will complete a self-assessment questionnaire about their continence disorder and their digestive symptoms, including the Rome 3 criteria. Each patient will also undergo a medical examination during which a questionnaire about their medical and surgical histories, current treatments, including contraceptive treatments, will be completed. A clinical examination will also be performed. Patients with anal incontinence will not undergo a comprehensive continence assessment (anorectal manometry, endoanal ultrasound, electrophysiologic tests) because flatus incontinence is often refractory to treatments that are usually indicated for fecal incontinence and because such an assessment will not be helpful in choosing the most appropriate treatment.

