**3.6 Study design and randomization**

All patients referred for flatus incontinence will undergo a glucose breath test. In the event of a positive glucose breath test, the patients will be asked to complete a 3-day bowel diary prior to randomization.

The patients will receive:

- Metronidazole (Flagyl^®^ per os, 500 mg, 3 per day for 10 days), or
- Carbosylane^®^ (45 mg of simethicone and 140 mg of activated charcoal per capsule, 3 capsules per day for 10 days.

The choice of antibiotic was empirical because of the small number of studies investigating the efficacy of antibiotics for treating SIBO and the lack of consensus. Large spectrum antibiotics appear to be the most appropriate antibiotics since they are effective against both aerobic and anaerobic bacteria. Rifaximin appears to be more effective than tetracycline and is not absorbed after oral ingestion, limiting the secondary effects. Unfortunately, rifaximin is not commercially available in France. One controlled study has shown that metronidazole is more effective than rifaximin in reducing the symptoms of SIBO and returning glucose breath test results to normal values [Di Stefano, 2005]. Another controlled study, which compared norfloxacin, clavulanic acid-amoxicillin, a probiotic, and a placebo [Attar, 1999] showed that norfloxacin and clavulanic acid are more effective for treating diarrhea in patients with SIBO than other treatments. Norfloxacin and metronidazole are the most frequently used antibiotics in France for treating SIBO. The minor and moderate secondary effects of norfloxacin and metronidazole are comparable in frequency. However, norfloxacin causes more frequent serious secondary effects than metronidazole, which is why we opted for metronidazole.

A symptomatic evaluation and a glucose breath test (for patients in the group receiving metronidazole) will be performed after the 10-day treatment.

Patients treated with Carbosylane^®^ may be given a course of antibiotics at the end of the study in the event they have persistent digestive symptoms. The results of this antibiotic treatment will not be taken into consideration for the purposes of the study.

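### The percentage-decrease primary outcome in 3.6 is undefined when the baseline diary is zero, and no entry condition requires a recorded gas leakage

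*Protocol*

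**What the plan says.** Entry under Protocol 3.2 rests on referral for "isolated or predominant (in the case of associated fecal incontinence) flatus incontinence", a positive glucose breath test and administrative conditions. None of the 5 inclusion criteria in 3.2 or the 12 exclusion criteria in 3.3 sets a minimum frequency of gas leakage. The one frequency limit, in 3.4, concerns stool rather than gas: "occasional fecal incontinence episodes with fewer than one episode per month".

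Under 3.6, after a positive breath test, "the patients will be asked to complete a 3-day bowel diary prior to randomization". Nothing is required of the count it records.

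The outcome is worded in three places:

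- 3.1: "The main outcome measure will be the daily number of gas leakages".
- 3.6: "The main primary outcome will be the percentage decrease in the mean daily number of gas leakages reported in the 3-day diaries", followed by "A positive clinical response will be defined as a greater than 50% reduction in the mean daily number of gas leakages".
- 4.3: "The difference between the mean number of flatus incontinence episodes before and during the treatment and the percentage decrease" are both to be calculated and compared between the groups.

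**The concern.** A percentage decrease has the baseline count as its denominator. If the three diary days contain no leakage, the percentage does not exist. The responder definition in 3.6 fails too, since a count of zero cannot fall.

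Such a patient meets every entry condition as written. Once the patient is randomised, the 3.6 outcome can only be left missing or given a value by convention. A statistical analysis plan could choose between these, but it cannot set eligibility. The data that would prevent the problem are in hand before allocation, and the protocol does not use them.

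The trial is small, so a few such patients count. The target is 20 per arm, and 4.1 assigns the extra recruits to non-compliance, allergy or intolerance, and loss to follow-up, not to an outcome that cannot be computed.

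**Working it through.** **The plan's own figure.** Section 4.1 keeps 20 per arm by recruiting 25. This is consistent with 20 / (1 − 0.20) = 25, a 20% loss that is implied and not stated. The 20 is declared arbitrary, so there is no power calculation to reproduce.

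**The logical step.** Let B and E be the mean daily leakages in the baseline and end-of-treatment diaries.

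- Percentage decrease (3.6) = 100 × (B − E) / B, undefined at B = 0.
- Response (3.6) requires a reduction of more than 50%, impossible at B = 0.
- Daily number (3.1) = E, computable at B = 0.
- Absolute difference (4.3) = B − E, computable at B = 0, but then zero or negative, so it cannot show improvement.

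Nothing in 3.2 to 3.4 or 3.6 rules out B = 0. This part needs no assumption.

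**How often.** The protocol gives no leakage rate, so the rates below are assumed. Let r be the mean number of leakages per day.

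- Common Poisson rate: P(zero in 3 days) = exp(−3r).
- Rates varying widely between patients (negative binomial, k = 1): P(zero in 3 days) = 1 / (1 + 3r).
- Chance of at least one zero baseline among 40 patients, Poisson: 1 − (1 − p)^40, with p the Poisson share.

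| r per day | Poisson share | Expected of 40 / of 50 | At least one of 40 | Negative binomial share | Expected of 40 / of 50 |
|---|---|---|---|---|---|
| 0.5 | 22% | 8.9 / 11.2 | near 100% | 40% | 16 / 20 |
| 1 | 5.0% | 2.0 / 2.5 | 87% | 25% | 10 / 12.5 |
| 2 | 0.25% | 0.10 / 0.12 | 9.5% | 14% | 5.7 / 7.1 |
| 3 | 0.01% | about 0 | 0.5% | 10% | 4.0 / 5.0 |

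**Effect of an entry rule of at least one diary leakage.** B is then at least 1/3 per day, so the percentage and the response are defined for every randomised patient who returns the end diary.

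**Screening cost of that rule.** Section 4.1 presumes that one patient in three tests positive, so 50 randomised patients need 3 × 50 = 150 tested. With the rule, the number is 150 / (1 − p):

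- Poisson, 1 per day: 150 / 0.9502 ≈ 158.
- Poisson, 0.5 per day: 150 / 0.7769 ≈ 193.
- Negative binomial, mean 1 per day: 150 / 0.75 = 200.

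**Regression to the mean.** Selecting on the baseline diary raises its expected count with no true change. At 0.5 per day (Poisson) the 3-day expectation goes from 1.5 to 1.5 / 0.7769 ≈ 1.93. At 1 per day it goes from 3 to 3 / 0.9502 ≈ 3.16. Because the selection precedes randomisation, it affects both arms alike.

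**The case against.** **The frequency is assumed.** Patients are referred for this symptom, and most probably leak often. At a common rate of 2 per day, 0.1 of 40 patients would have a zero baseline; at 3 per day, practically none. This stands: the size is unknown and may be negligible. Against it, referral does not guarantee a leakage on three particular days, and a moderate average does not protect if patients differ widely.

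**The trial would still have an outcome for these patients.** A reader might infer that a zero-baseline patient contributes nothing to the main comparison and must be dropped. The protocol does not support that. Section 3.1 names the daily number and 4.3 also compares the absolute difference, and both can be computed. What is lost is the form that 3.6 calls the main primary outcome, and the response based on it.

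**Handling belongs in the analysis plan.** The treatment of an undefined percentage may be specified in an analysis plan that is not shown. It therefore cannot be said that the choice would be made after seeing the data. That plan could still only repair the problem after randomisation; the absent entry condition is a protocol matter.

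**Another remedy exists.** Making the count or the absolute difference primary would remove the undefined value without turning anyone away. This is a legitimate alternative, but it changes the primary outcome stated in 3.6, and a patient who starts at zero still cannot show improvement.

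**The cost rises with the problem.** If many patients have zero baselines, the rule turns many away; if few do, it changes little. This stands, and the extra testing has to be counted as a cost.

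**Conclusion.** The point holds in a limited form. It is certain from the text that a patient with no leakage in the baseline diary can be randomised, and that the 3.6 percentage and response are then unavailable for that patient. The 3.1 and 4.3 measures are not affected in this way.

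How often this would happen cannot be settled from the protocol. Over assumed common rates of 0.5 to 2 per day the share runs from 22% to 0.25%; at means of 1 and 2 per day it would be 25% and 14% if rates vary widely (k = 1). Severity is minor to moderate: the gap is definite, its frequency unknown, and prevention is simple.

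A reader might also expect an entry rule to cure the instability of percentages built on one or two leakages in three days. It does not; it removes only the undefined values.

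**What to change.** State in 3.2, and repeat in 3.6 at the point of randomisation, that a patient is randomised only if the pre-randomisation 3-day diary records at least one gas leakage. No higher threshold is needed to make the outcome computable.

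The rule needs no new visit or data item, and the 20 and 25 per arm can stay. Its costs are:

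- Breath-test-positive patients with no diary leakage are not randomised, so more patients may have to be tested: about 158 at 1 per day or 193 at 0.5 per day, instead of 150, and more if rates vary widely.
- A slight regression to the mean inflates the fall within each arm. It does not favour either arm, but within-arm falls should be read with it in mind.
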